### Recuitment {15}

We use a number of strategies to achieve the target sample size: We contact companies with shift work by email and ask them to forward our call for participation to their employees. As there has been little response so far to this strategy, we are now increasingly using telephone contact. We are also mailing to several thousand doctors in Germany and Austria: General practitioners, psychiatrists, and occupational physicians. Some of them have asked for printed flyers.

The study will also be promoted through social media (Facebook, Instagram). Printed flyers will also be distributed (pharmacies, personal contacts, etc.). The fact that participants will receive free treatment for their sleep problems does not seem to be enough of an incentive. That is why we are now offering a financial compensation of 50 euros per participant. We hope to get more feedback on this.

## Methods: assignment of interventions (for controlled trials)

### Allocation {16a-c}

To randomly assign subjects to groups, participants will be numbered consecutively by the study management in the order of their enrolment. The trainers use a computer-generated random number sequence and match these numbers to the participants’ sequential number sequence. The final allocation of participants to conditions is made by the study management.

There is allocation concealment, as only number sequences are used in the allocation process, and no one is able to assign a name to a number.

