### Eligibility criteria {10}

Included are people of all genders, aged 18 to 65, who work shifts for at least 30 h a week and suffer from primary insomnia. We excluded people with pre-existing physical conditions such as sleep apnoea, restless legs syndrome or chronic pain. We also excluded people with a history of mental disorders, namely severe affective or anxiety disorders, acute substance abuse disorders, and psychotic or schizo-affective disorders.

The assessment of the inclusion criteria by means of interviews and the implementation of the interventions will be carried out by psychology master students from the University of Salzburg, who already have clinical experience and have undergone specific training.

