### Interventions {11a}

Treatments in both conditions are delivered online by MS Teams in groups of 12 people with one trainer per group. Both conditions receive seven sessions over 7 weeks of 90 min each. As a starting point, the CBT-I-S group receives reading information material 1 week before the first session. The standard CBT-I condition starts keeping a sleep diary 1 week before the first session.

The implementation will start when enough participants have been found for two parallel groups per condition, to be able to take an alternative appointment in the parallel group in case of scheduling problems.

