### Limitations

A limitation of this study is that it is an online-only study. This decision was made under the impression of the corona pandemic, but also for purely practical reasons: 142 shift workers with sleep disorders are probably difficult to find in the Salzburg area, and face-to-face appointments plus travel could become a problem for shift workers. By opting for online delivery, we can extend the recruitment process nationally and save participants travel time.

However, there is a risk that less group cohesion will develop in this setting, especially if people come from completely different regions (e.g., North Rhine-Westphalia/Germany vs. Vorarlberg/Austria). There could be mentality and language problems here. The trainers are prepared for this during their training.

The inclusion of different professional groups has not only advantages. It is possible that the severity of the sleep disorder or the exact, individual symptoms differ between professions. An example is the police and fire services (sometimes traumatising) compared to manufacturing jobs (monotonous). This could affect both group dynamics and the effectiveness of therapy. The data need to be used to check whether subgroups need to be formed here.

Another limitation is the fact that the therapies are carried out by trained students. It would of course be better to use experienced psychotherapists with additional, specific training in sleep disorders. Unfortunately, this is not possible for financial reasons.

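### The stated reason for allocation concealment conflicts with the allocation procedure, and that procedure does not assure concealment

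*Protocol article*

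**What the plan says.** Allocation {16a-c} describes three steps and one claim.

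- Numbering: "participants will be numbered consecutively by the study management in the order of their enrolment".
- Matching: "The trainers use a computer-generated random number sequence and match these numbers to the" sequential numbers of the participants.
- Placement: "The final allocation of participants to conditions is made by the study management".
- Claim: concealment is said to hold because "only number sequences are used in the allocation process, and no one is able to assign a name to a number".

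Other sections say who the trainers are. Under Eligibility criteria {10}, "The assessment of the inclusion criteria by means of interviews and the implementation of the interventions will be carried out by psychology master students". Interventions {11a} has treatment delivered "in groups of 12 people with one trainer per group". The Limitations section adds that "the therapies are carried out by trained students".

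Blinding {17a-b} states that there is none.

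**The concern.** Concealment has two parts. Whoever decides on a person's enrolment must not be able to foresee the next assignment, and an assignment once made must not be open to change. Replacing names with numbers secures neither part. Here the sole reason given for concealment is the use of numbers, and the same section gives the key to those numbers to the party that makes the placement.

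The eligibility decision leaves room for foreknowledge to act. It includes a judgement on whether an affective or anxiety disorder is severe (Eligibility criteria {10}), and concurrent therapy for other reasons is decided case by case ({11d}).

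The stakes are higher than usual for three reasons:
- The trial is open to trainers and participants, and its outcomes are mainly self-reported (Data collection methods {18a}).
- The team tests its own manual and expects it to be superior (Objectives {7}).
- The analysis is per protocol, among those who attended at least 4 sessions (Statistical methods {20 a-c}). The randomised comparison is thus already weakened after allocation.

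**Working it through.** No formula applies to the allocation procedure, so the check sets the sections side by side. The one design figure, N = 142 in Sample size {14}, does reproduce. With effect 0.1, 3 measurement times and correlation 0.7, the noncentrality is 0.1² × 142 × 3 / (1 − 0.7) = 14.2. On 2 and (142 − 2) × 2 = 280 degrees of freedom at level 0.01, power is 0.803. The point below neither depends on that figure nor changes it.

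**Step 1: who can link a person to a number?** The study management issues the numbers as people enrol, and later places people in conditions. To invite a given person to a given group it must know which person carries which number. The statement that nobody can make this link is therefore false for the study management on the section's own terms.

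**Step 2: does another section restore the claim?** Data management {19} uses a self-made subject code and stores no names with the data after pre-screening. That separates names from questionnaire answers. It does not separate names from the enrolment list or the allocation list. Under {18b}, participants are reminded by e-mail and then by telephone, so identities are kept somewhere.

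**Step 3: who holds the sequence, and who screens?** Trainers match the sequence (Allocation {16a-c}). Trainers lead the treatment groups (Interventions {11a}). Treatment is given by students (Limitations), and the students also hold the eligibility interviews (Eligibility criteria {10}). At role level, then, the people who judge eligibility and the people who handle the sequence come from one pool. Because numbers follow enrolment order, a trainer who also interviews could infer who stands behind a number. The text does not say that the same individual does both for a given participant.

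**Step 4: could an assignment be foreseen?** This depends on whether the sequence exists while people are still being enrolled, and the section does not say. If it exists, someone who sees it and knows the next free number can foresee that assignment. If it is generated only after the whole wave has been enrolled, nobody can.

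**Step 5: could an assignment be changed?** The placement by the study management comes after the matching. The section neither describes discretion at this step nor makes the matched result binding.

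**Step 6: is there any other safeguard?** The section names no holder of the sequence who is separate from screening and treatment, and no lock on the result.

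**The case against.** The strongest reply is that duties are divided. One party holds the link between person and number, and another applies the sequence to bare numbers. On this reading the trainers never see names, and the last step by the study management merely carries out the match, since someone has to put people into groups. The steps are also listed with numbering before matching. Treatment starts only when two groups per condition can be filled (Interventions {11a}), and the Strengths section reports several weeks between enrolment and start for some participants. Matching a whole wave after enrolment is a natural reading, and it would close the route through foreknowledge.

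Much of this stands. Foreseeability depends on a timing that the text leaves open, discretion at the placement step is an inference, and the overlap of trainers and interviewers is shown only for the role. The reply does not rescue the stated reason for concealment, which remains contradicted, and it relies on a timing and a binding result that the section does not state.

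A reader might infer three stronger things that the document does not support:
- **That allocation was in fact steered.** Nothing in the text shows this.
- **That the procedure cannot give equal arms as promised in Trial design {8}.** This would need an unrestricted sequence, and the text does not say that it is unrestricted. A random ordering split in half gives equal arms, and blocking detail is commonly left to the full protocol.
- **That the bias can be expressed as a share of the planned effect.** This would need an assumed proportion steered and an assumed prognostic gap. It would also set a baseline difference against a group-by-time effect, and the two are not the same quantity.

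It is also fair to say that randomisation is not the only protection. Data are collected online to limit evaluator influence, and the pre-treatment measurement would reveal imbalance in what is measured. It would not reveal imbalance in what is not measured.

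**Conclusion.** The point holds in this form: the sole reason given for concealment is contradicted within its own section and would not secure concealment even if it were true. The procedure as written does not exclude foreknowledge during enrolment or a change after matching, and it is not evidence that either occurred.

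The contradiction about the study management follows directly from the text. The overlap between screening and sequence handling is a sound inference at role level only. The size of any resulting bias cannot be computed from the document, and none is claimed here. It should still be put right before further participants are allocated, because a core safeguard is asserted without support in an unblinded trial with mainly self-reported outcomes.

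**What to change.** **For waves not yet allocated.**
1. Complete eligibility and the t1 measurement for everyone in the wave.
2. Generate the 1:1 allocation for the whole wave in one step with a seeded script, run by an existing project member who neither screens nor treats.
3. Archive the seed and the output with a date, and treat the list as final.
4. Remove the trainers' matching step and limit the study management to carrying out the list.

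A co-supervisor could take on step 2 if not involved in screening or treatment. As a planned author of the results (Dissemination policy {31 a-c, 33}), that person would not be fully independent, which is a further reason to archive the seed.

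**For waves already allocated.** Document who generated the sequence, when this was done relative to enrolment, who could see it, and whether any placement differed from the match. An amendment cannot change these waves, and the document does not say how many there are.

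**In the text.** Replace the concealment sentence with a statement of who generates the list, at what point, and that it is binding.

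**Cost.** A short amendment and no new staff. Treatment already waits for two groups of 12 in each of two conditions, which is 2 × 2 × 12 = 48 people per wave, or 142 / 48 ≈ 3 waves in all. Randomising a wave once it is assembled should therefore add no delay. Seven weekly sessions plus the preparatory week make up the 8 weeks from t1 to t2 (Participant timeline {13}), so taking t1 before allocation fits the existing schedule. The sample size does not change.

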### Blinding {17a-b}

There is no blinding. Both trainers and participants know which group they are in.

## Methods: data collection, management, and analysis

### Data collection methods {18a}

The data collection is done online to avoid the influence of the evaluators. As we primarily use self-report questionnaires, socially desirable responses cannot be excluded. An attempt is made to minimise this bias by providing appropriate information in the questionnaire instructions. Missing data are avoided by making all questions mandatory.

Below is a description of the integrated questionnaires according to primary and secondary outcomes. The interpretation of Cronbach’s alpha values follows George and Mallery [39].

#### Primary outcomes

PSQI: Pittsburgh Sleep Quality Index [40, 41]. This questionnaire measures sleep onset latency, total sleep time and subjective sleep quality. The re-test reliability is good, *r* = 0.82–0.89 [40], Cronbach’s *α* is also good with a value of 0.80 [41], the diagnostic validity is over 80% (sensitivity) or between 83 and 87% (specificity; quoted from [40]). So it can also be considered good.ESS: Epworth Sleepiness Scale [42], to measure daytime sleepiness. Cronbach’s α is acceptable to good with values between 0.73 and 0.88. According to Kendzerska et al. [43], re-test reliability is only described as good by one study with a value of *r* = 0.82, other studies found lower values. In their meta-analysis, Kendzerska et al. [43] found medium validity.ISI: Insomnia Severity Index [44], to assess severity of sleep disorder. According to [45], quality criteria are overall acceptable to good: Cronbach’s *α* = 0.74–0.78. In the opinion of these authors, further findings on concurrent validity and reliability are evidence that it is a valid and sensitive instrument.

#### Secondary outcomes

HADS-D: Hospital Anxiety and Depression Scale [46] to measure anxiety and depressive mood. Test quality criteria are predominantly good: Internal consistency: Cronbach’s alpha, patient sample *α* = 0.80 (anxiety), *α* = 0.81 (depression). Re-test reliability: *r* = 0.69–0.89 (anxiety) or *r* = 0.85 (depression). Convergent validity: *r* = 0.54–0.77 [46, 47].MZS: Dysfunctional sleep attitudes (Opinions about sleep questionnaire, based on the Dysfunctional Beliefs and Attitudes about Sleep, DBAS-16; [48]), measures dysfunctional and irrational beliefs about sleep. Weingartz and Pillmann [48] state that the internal consistency is good, with a Cronbach’s alpha = 0.87, and they describe the validity and reliability as sufficient to good.PSAS: Pre-Sleep Arousal Scale [49]. Measures cognitive and physiological arousal in the 2 h before falling asleep. In a doctoral thesis by Vochem [50], the internal consistency is described with reference to the original [51] as follows “…for healthy sleepers on the physical arousal subscale as good (0.84) and on the cognitive arousal subscale as questionable (0.67),” “for insomnia patients as acceptable (0.76) and good (0.81).” ([50], p. 47). Retest reliability (3 weeks) is reported by the original authors [51] as *r* = 0.72 for the cognitive subscale and *r* = 0.76 for the somatic subscale.Own item: “Do you like working shifts?” to measure attitudes towards shift work.

### {18b}

In order to keep the dropout rate low, the trainers have to emphasise the importance of data collection in the group sessions. The subjects are first reminded of the measurement times by e-mail. If this is not sufficient, a phone call follows. The offer to take part in the most effective therapy after data collection is intended to provide an incentive to take part in the follow-up measurement. A further incentive for participants not to drop out of the study or the data collection prematurely is the 50 Euro compensation for effort, which will only be paid out at the end of the study.

### Data management {19}

As the data is collected online, no data entry is required. The subjects have already defined a subject code for themselves at the pre-screening stage, following precise instructions. This consists of the first letter of the mother’s first name, the first letter of the mother’s maiden name and the day of the mother’s birthday. This code is used to store and process the data. After pre-screening, no further names are stored with the data. The data will be collected using LimeSurvey and only exported to SPSS in pseudonymised form for processing.

Data quality is promoted through plausibility checks: For each variable, it is checked whether the participants’ answers are within a plausible range.

The raw data is stored both in LimeSurvey and in an exported SPSS file. In addition to a local PC, the processed data is stored on an external hard drive as a backup. The required retention period is 7 years.

### Statistical methods {20 a-c}

For analysing primary and secondary outcomes, we will use linear mixed-models:

We will make within-subject comparisons of the primary and secondary outcomes at the three time points before and after treatment and at follow-up. We will also make between-subject comparisons, i.e., a comparison of the three conditions at the three time points.

Mediator and moderator analyses of the moderation and mediation of the outcomes: No hypotheses about mediators and moderators will be formulated. These analyses are purely exploratory.

We expect low attrition at the post-measurement, but somewhat higher at the follow-up measurement. Individuals who did not complete the post-measurement will be excluded. Those who did not complete only the follow-up may be included in the pre-post comparison but must be excluded from the calculations of the stability of the effects. Depending on their number, it may be necessary to analyse whether they represent a group with specific characteristics. As no post- or follow-up data is expected to be available from the dropouts, an intention-to-treat analysis is not possible. Instead, a per-protocol analysis will be conducted with all participants who were present in at least 4 sessions.

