### Trial design {8}

The trial will be conducted in two parallel groups with controlled randomised allocation of the same number of subjects per group. The aim is to prove the superiority of the newly developed therapy (CBT-I-S) over standard therapy (CBT-I). Originally, an active control group was planned to keep a sleep diary for the same time period (8 weeks). Unfortunately, due to difficulties in recruiting subjects, this group had to be cancelled.

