### Outcomes {12}

The primary outcome is improvement in the following key sleep variables: total sleep time, sleep onset latency, subjective sleep quality and daytime sleepiness. We also want to measure the severity of the sleep disorder.

Secondary outcomes are improvements in depressive mood and anxiety, dysfunctional sleep attitudes, and cognitive and physiological arousal.

Data will be collected at three time points: before starting treatment, at its end and 6 months later as a follow-up. We will compare group means between groups and within groups at each time point. Since we will have multiple primary outcomes over multiple time points, we will adjust the α-level using a Bonferroni correction.

The magnitude of the differences, especially in the pre-post comparisons, should not only be statistically, but also clinically significant. This means, for example, that subjects no longer meet the criteria for a sleep disorder (DSM-5, [11]) after treatment.

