### Sample size {14}

To determine the required sample size, a power estimation was carried out with G*Power [38]: ANOVA with repeated measures and within-between interactions, 2 groups and 3 measurement times, small expected effect 0.1, desired power of 0.80 (1-β), *p* = 0.01 (4 outcome variables), correlation among repeated measures 0.7 results in a total sample size of *N* = 142.

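### The analysis text still has three conditions and compares group means at each time point, while the sample size rests on a two-arm group-by-time interaction that the analysis text never names; depending on the contrast meant, power runs from about 47% to 82%

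*Protocol article*

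**What the plan says.** All references are to the protocol article.

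- **Trial design {8}**: "The trial will be conducted in two parallel groups with controlled randomised allocation of the same number of subjects per group". The same section says that a planned control group was cancelled because recruitment was difficult, and that the aim is to show superiority of CBT-I-S over CBT-I. The Abstract and Strengths sections also describe two arms.
- **Sample size {14}**: "ANOVA with repeated measures and within-between interactions, 2 groups and 3 measurement times, small expected effect 0.1", with power 0.80, p = 0.01 and a correlation among repeated measures of 0.7, giving N = 142.
- **Outcomes {12}**: "We will compare group means between groups and within groups at each time point". A Bonferroni correction is to cover the multiple primary outcomes and time points; the number of tests is not given.
- **Statistical methods {20 a-c}**: linear mixed models for all outcomes, with within-subject comparisons over the three times and between-subject comparisons described as "a comparison of the three conditions at the three time points".
- **Objectives {7}**: the superiority is expected to last for 6 months after treatment.

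Neither {12} nor {20 a-c} mentions the group-by-time interaction, and neither says how the pre-treatment value enters the comparison between arms.

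**The concern.** There are two defects. The first is a plain contradiction: the analysis section has three conditions and the trial has two. According to Protocol amendments {25} and Trial status, the cancellation was submitted on 21 October 2023, the date of protocol version 2, so the current analysis text was not brought into line with the current design.

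The second is a mismatch between the test that was sized and the comparison that is described. The interaction test gains precision from the 0.7 correlation because each participant serves as his or her own reference. A comparison of raw means at a single time gains nothing from it. Taken literally, the wording also includes a between-arm test at pre-treatment, which only checks randomisation and could take a share of the Bonferroni correction. The interaction has 2 degrees of freedom and by itself shows neither which arm is better nor when, so a superiority claim needs a directional contrast as well. The article names none that is tied to the power calculation.

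At stake is whether the trial delivers the 80% power it states, and whether the deciding contrast is fixed before the data are seen.

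**Working it through.** **Inputs.** From {14}: 2 groups, m = 3 times, f = 0.1, alpha = 0.01, power 0.80, rho = 0.7, N = 142. From {8}: equal allocation, so 71 per arm. From {7}: a stable effect, so arm differences of (0, d, d) at pre, post and follow-up. Assumptions: unit SD at each time, two-sided tests, all 142 analysed, no clustering by therapy group.

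**1. The plan's own figure.** For the interaction, lambda = N·f²·m/(1 − rho) = 142 × 0.01 × 3/0.3 = 14.2, with 2 and (142 − 2) × 2 = 280 degrees of freedom. The noncentral F gives power 80.3%; N = 140 gives 79.6%. So 142 reproduces exactly.

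**2. What f = 0.1 means in SD units.** With arm difference d_t at time t, f² is the mean over times of ((d_t − mean d)/2)².

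- Stable (0, d, d) or post-only (0, d, 0): f² = d²/18, so d = 0.1 × √18 = 0.424.
- Linear growth (0, d/2, d): f² = d²/24, so d = 0.1 × √24 = 0.490.

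**3. Power of a single-time contrast.** Two-sample t, noncentrality = d·√(71/(2v)), 140 degrees of freedom, critical value 2.611 at alpha 0.01. The variance factor v is 1 for raw means, 2(1 − 0.7) = 0.6 for change from baseline, and 1 − 0.7² = 0.51 for baseline adjustment. With d = 0.424:

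| Contrast | Noncentrality | alpha 0.01 | alpha 0.005 |
|---|---|---|---|
| Raw means | 2.528 | 46.9% | 38% |
| Change from baseline | 3.263 | 74.2% | 66% |
| Baseline-adjusted | 3.540 | 82.2% | 75% |

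The raw contrast has 1/0.51 = 1.96 times the variance of the adjusted one. Raw means would need about 264 participants (132 per arm) for 80% power at alpha 0.01.

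**4. Sensitivity to the correction.** The article does not count its tests. With d = 0.424, raw and adjusted power are 50% and 84% at 0.05/4 = 0.0125, 41% and 78% at 0.05/8, and 35% and 73% at 0.05/12.

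**5. Sensitivity to the pattern.** Under linear growth (0.245 SD at post, 0.490 SD at follow-up), alpha 0.01:

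| Contrast | Post | Follow-up |
|---|---|---|
| Raw means | 13% | 62% |
| Change from baseline | 24% | 87% |
| Baseline-adjusted | 29% | 93% |

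**6. A difference of 0.2 SD.** The sized interaction test has about 15% power if the difference is stable (lambda = 142 × (0.04/18) × 3/0.3 = 3.16) and about 10% if it grows linearly (lambda = 142 × (0.04/24) × 3/0.3 = 2.37).

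**The case against.** The strongest reply is that the article commits to linear mixed models over all three measurements. Such a model with arm, time and their interaction yields the sized test directly, and the within- and between-subject comparisons can be read as contrasts inside it. Exact fixed effects, the baseline covariate and the choice of contrast are commonly left to an analysis plan. This stands. A reader might infer that the trial will be analysed without baseline adjustment and therefore has 47% power instead of 80%. The documents do not support that: they are silent on adjustment, and 47% belongs to one literal reading, under a stable or post-only effect, alpha 0.01 and no losses.

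A second reply is that f = 0.1 is labelled small by convention. That also stands as a matter of labelling. The article gives no benchmark for a meaningful difference between the two treatments, so nothing in it shows that 0.42 SD is too large to expect. The conversion is still needed if readers are to know what the trial can detect.

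A third reply is that the pre-treatment comparison may not count in the Bonferroni family. The article gives no count, so this stays open.

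The replies do not remove the three-condition wording. Nor do they remove the fact that the comparison is described twice and neither time as the test that was sized. That goes beyond omitted detail.

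**Conclusion.** The point holds in a limited form. The count of conditions is wrong in the current text. The comparison described differs from the one sized, and the text admits readings whose power at the implied effect runs from about 47% (raw means at one post-baseline time) through 74% (change from baseline) to 82% (baseline-adjusted), with 80% for the interaction itself. These figures rest on a difference of 0.424 SD that is stable or present only at post, alpha 0.01, correlation 0.7 and 71 analysed per arm. Stricter alpha or attrition lowers the single-time figures, and a different time course moves them in either direction. The trial's size is not shown to be wrong, since 142 reproduces. The text should be corrected, but this is not a fatal flaw.

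**What to change.** 1. In {20 a-c}, change three conditions to two.
2. In {12} and {20 a-c}, name the confirmatory superiority test, for example: *the CBT-I-S minus CBT-I difference at post-treatment from a linear mixed model with arm, time and arm-by-time, adjusted for the pre-treatment value (or with the arms constrained equal at pre-treatment); the same contrast at follow-up tests durability.*
3. Drop the between-arm test at pre-treatment.
4. In {14}, state that f = 0.1 corresponds to an arm difference of about 0.42 SD (stable or post-only effect) to 0.49 SD (linear growth). Add that about 80% power holds at alpha 0.01 with 71 analysed per arm, that the adjusted 0.42 SD contrast has about 75% at alpha 0.005, and that attrition lowers both.

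**Cost.** No new data are needed, because the pre-treatment value is already collected. It is more than a wording change, though: naming post-treatment as the deciding time fixes the estimand. If the effect grows linearly to follow-up, the adjusted post-treatment contrast has about 29% power, against 80% for the interaction. If the sponsor thinks a late effect likely, it should weigh that before choosing the time point, and record the choice before the data are analysed.

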**Methods:**

A randomised controlled trial with *N* = 142 will be conducted to compare two conditions: the newly developed therapy manual will be carried out in the experimental group, while cognitive behavioural therapy for insomnia will be employed in the standard group. Both treatments will be conducted online via MS Teams in a group setting with seven sessions each. Data will be collected at three measurement points (pre, post, 6-month follow-up) and analysed using linear mixed models. The study will investigate whether the two treatments have led to significant improvements in total sleep time, sleep onset latency, subjective sleep quality and daytime sleepiness in shift workers. It will also examine whether the new therapy manual is superior to standard therapy in shift workers and whether these effects are stable.

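### The sample size of 142 has no allowance for the losses the plan expects and the exclusions it prescribes, so the stated 80% power does not hold for the three-time-point analysis

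*Protocol article*

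**What the plan says.** Protocol article, Sample size {14}: the calculation is a G*Power run for "ANOVA with repeated measures and within-between interactions, 2 groups and 3 measurement times", with effect size 0.1, power 0.80 and a significance level of 0.01 justified by four outcome variables. It closes with "correlation among repeated measures 0.7 results in a total sample size of" 142. Neither a dropout rate nor an inflation step is mentioned.

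The same 142 is used as the size of the trial. The Abstract says a randomised trial of 142 "will be conducted to compare two conditions", the Strengths section calls 142 the planned sample size, and the Limitations section explains online delivery by the difficulty of finding 142 shift workers locally.

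Statistical methods {20 a-c}: "We expect low attrition at the post-measurement, but somewhat higher at the follow-up measurement". Three removals follow:
- People without the post-measurement (t2) are excluded.
- People who miss only the 6-month follow-up (t3) may stay in the pre-post comparison but "must be excluded from the calculations of the stability of the effects".
- The section declares an intention-to-treat analysis impossible and limits the analysis to people who attended at least four sessions.

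**The concern.** The two sections do not fit together. Sample size {14} needs 142 people measured at all three times. Statistical methods {20 a-c} starts from 142 recruited people, predicts that some will be lost and prescribes removing others. If 142 is the bare minimum for 80% power, any loss takes the analysed set below the stated power. What is at stake is whether a reader can take the 0.80 as describing the analysis that will be run. The question for the check is whether 142 contains a hidden reserve and, if not, how large the shortfall could be.

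**Working it through.** **Inputs from Sample size {14}:** k = 2 groups, m = 3 times, effect size f = 0.1, "correlation among repeated measures 0.7" (ρ), α = 0.01, target power 0.80. Equal allocation comes from Trial design {8}. Sphericity is assumed, as the article names no correction.

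**Formula** (repeated-measures ANOVA, within-between interaction, noncentral F):

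- λ = f² × N × m / (1 − ρ)
- df1 = (k − 1)(m − 1) = 2
- df2 = (N − k)(m − 1)
- power = P(F′(df1, df2, λ) > F critical at α)

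**Step 1: reproduce the plan's figure.** For N = 142, λ = 0.01 × 142 × 3 / 0.3 = 14.2 and df2 = 140 × 2 = 280, which gives power 0.803. For N = 141, power is 0.7995; for N = 140, it is 0.796. So 142 is reproduced exactly and is the smallest total that reaches 0.80. At the stated α it contains no reserve. The formula counts each participant as measured at all three times.

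**Step 2: power in a reduced set.** The article gives no loss rate, so the combined loss below (no t2, no t3 or fewer than four sessions) is an assumption, shown as a range. The analysed number is 142 × (1 − loss), rounded.

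| Assumed combined loss | N analysed | λ | df2 | Power at α = 0.01 |
|---|---|---|---|---|
| none | 142 | 14.2 | 280 | 0.803 |
| 5% | 135 | 13.5 | 266 | 0.776 |
| 10% | 128 | 12.8 | 252 | 0.747 |
| 20% | 114 | 11.4 | 224 | 0.680 |
| 30% | 99 | 9.9 | 194 | 0.595 |

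**Step 3: the same shortfall as a detectable effect.** λ is proportional to f² × N and the critical value barely moves over this range. The effect detectable with about 80% power is therefore close to 0.1 × √(142 / N): 0.103 at 135, 0.105 at 128, 0.112 at 114 and 0.120 at 99.

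**The case against.** Several counter-arguments deserve a fair hearing.

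- **The calculation is correct.** This stands. The stated inputs give 142; the gap is a missing planning allowance, not an arithmetic error.
- **Losses may be small.** The text expects low attrition at t2 and only somewhat more at t3. Reminders, phone calls, a payment withheld until the end of the study and alternative appointments in parallel groups all support retention. This stands as a limit on size: at 5% loss the drop is under 3 points (0.803 to 0.776), and nothing in the article points to 30%. But these measures create no reserve, and the article itself still expects losses.
- **The 0.01 is stricter than 0.05 / 4 = 0.0125.** At 0.0125 the required N is 136, so 142 would carry a reserve of six (6 / 142 = 4.2%). A 5% loss would use it up (0.799), and 10% would give 0.77. The article states 0.01, so this helps only a little.
- **People missing only t3 stay in the pre-post comparison.** True, but the sample size was computed for three times. With the same f, ρ and α, a two-time interaction (m = 2) has power 0.68 even with all 142, so keeping them there does not recover the stated 0.80.
- **Mixed models use partial data.** They can, but the section prescribes removing these people.

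A reader might also draw three stronger conclusions that the article does not support. First, the Strengths section's remark that 142 gives more statistical power might seem false. It is made in contrast with other shift-work studies, one of which is cited in the Background with N = 19, and it remains true at 128 or 114 analysed. Second, one might infer that a null result will be over-interpreted; nothing in the article says how a null result would be read. Third, one might add a stricter α to enlarge the shortfall. That is a separate multiplicity question and should not be counted as an effect of attrition.

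**Conclusion.** The point holds in a limited form. Under its own inputs, 142 is the minimum number of people with complete data, and it is also the number to be recruited. Because the plan expects losses and prescribes exclusions, the stated 0.80 does not hold for the three-time-point analysis. At α = 0.01 the shortfall is about 3 points at 5% loss, 6 at 10%, 12 at 20% and 21 at 30%. These sizes rest on assumed loss rates and on sphericity; only the absence of a reserve follows from the article alone. If losses turn out as low as the plan hopes, the practical effect is minor. It is worth correcting because the correction is cheap.

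**What to change.** In Sample size {14}, state the expected combined loss at t2 and t3, including people who fall below four sessions, and give its basis. Then restate the power at the resulting analysable number, or the effect detectable with 80% power at that number. If no rate can be justified, a short table like the one above would do.

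In Statistical methods {20 a-c}, let the linear mixed model that is already planned use all available data from randomised participants, so that people who miss only t3 are not dropped from the three-time-point analysis. This recovers part of the lost information, though not all of it.

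The cost is a sentence or small table, an edit to the exclusion rules and a less favourable stated power. No extra enrolment is asked for, which matters given the recruitment difficulties the article reports.
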